## Abstract

**Background:**

Persistent physical symptoms (PPS), also known as medically unexplained symptoms (MUS), affect approximately 50% of patients in secondary care and are often associated with disability, psychological distress and increased health care costs. Cognitive behavioural therapy (CBT) has demonstrated both short- and long-term efficacy with small to medium effect sizes for PPS, with larger treatment effects for specific PPS syndromes, including non-cardiac chest pain, irritable bowel syndrome (IBS) and chronic fatigue syndrome (CFS). Research indicates that PPS conditions share similar cognitive and behavioural responses to symptoms, such as avoidance and unhelpful beliefs. This suggests that a transdiagnostic approach may be beneficial for patients with PPS.

**Methods:**

A randomised controlled trial (RCT) will be conducted to evaluate the efficacy and cost-effectiveness of a transdiagnostic CBT-based intervention for PPS. 322 participants with PPS will be recruited from secondary care clinics. Participants stratified by clinic and disability level will be randomised to CBT plus standard medical care (SMC) versus SMC alone. The intervention consists of 8 CBT sessions delivered by a qualified therapist over a period of 20 weeks. Outcomes will be assessed at 9, 20, 40- and 52-weeks post randomisation. Efficacy will be assessed by examining the difference between arms in the primary outcome Work and Social Adjustment Scale (WSAS) at 52 weeks after randomisation. Secondary outcomes will include mood, symptom severity and clinical global impression at 9, 20, 40 and 52 weeks. Cost-effectiveness will be evaluated by combining measures of health service use, informal care, loss of working hours and financial benefits at 52 weeks.

**Discussion:**

This trial will provide a powered evaluation of the efficacy and cost-effectiveness of a transdiagnostic CBT approach versus SMC for patients with PPS. It will also provide valuable information about potential healthcare pathways for patients with PPS within the National Health Service (NHS).

**Trial registration:**

ClinicalTrials.gov NCT02426788. Registered 27 April 2015. Overall trial status: Ongoing; Recruitment status: No longer recruiting.

## Background

Medically unexplained symptoms (MUS) refer to persistent bodily symptoms cannot be adequately explained by organic pathology [1]. Although the umbrella term MUS is commonly used in health care, previous literature suggests that patients prefer the term *persistent physical symptoms (PPS)* [2]. For this reason, the patient-centred label PPS will be used throughout this paper to refer to MUS.

In secondary care, it is estimated that up to 50% of new referrals experience PPS [3]. These symptoms are often associated with profound functional impairment and psychological distress [3, 4]. Approximately 50% of patients with PPS present with co-morbid conditions, including anxiety, depression [3]. Left untreated, the prognosis of PPS patients is poor [1]. PPS are frequently seen in most medical specialties: irritable bowel syndrome (IBS) in gastroenterology, non-cardiac chest pain in cardiology, fibromyalgia (FM) in rheumatology, respiratory cough and breathlessness in respiratory medicine, and functional neurological symptoms in neurology [5]. Large amounts of healthcare and financial benefits go towards the diagnosis and treatment of PPS, with NHS costs amounting to approximately £3 billion per annum in the working population. Output losses due to sickness absence amounts to several billion [6]. Overall quality of life in people with PPS is poor with many not being able to do the things healthy people take for granted.

The management and treatment of patients with PPS is one of the most difficult tasks facing medical specialists in secondary physical healthcare services. An increasing body of evidence shows that cognitive behavioural interventions can be effective in reducing PPS severity and healthcare-related expenditures. Cognitive behavioural therapy (CBT) has been demonstrated to have both short- and long-term efficacy with small to medium effect sizes. Two meta-analyses examined the clinical effectiveness of short-term psychological therapies (including CBT, reattribution training, psychodynamic therapy, hypnosis etc.) for treating patients with PPS. The results indicated a beneficial effect of CBT for PPS [7, 8]. Improvements have also been reported for several specific PPS syndromes, including non-cardiac chest pain [9–11], IBS [12, 13], and chronic fatigue syndrome (CFS) [14]. However, more effective treatments undoubtedly need to be developed as effect sizes are at best modest. People with different PPS conditions often share similar cognitive and behavioural responses to symptoms, including fear avoidance beliefs and catastrophic misappraisal [1]. This suggests the possibility of transdiagnostic aetiological factors underlying these disorders, as well as common perpetuating processes and pathways.

There is an accumulating evidence base supporting the efficacy of transdiagnostic approaches for affective disorders. A transdiagnostic approach assumes that similar psychological processes maintain symptoms and disability across conditions. A previous systematic review and meta-analysis concluded that transdiagnostic approaches may be as effective as diagnosis-specific treatments for alleviating anxiety and may even be superior for treating depression. However these conclusions were based on a small number of studies [15]. Norton & Berra (2012) conducted a non-inferiority RCT comparing the efficacy of transdiagnostic CBT to disorder specific CBT for anxiety disorders. The results revealed treatment equivalence between transdiagnostic and disorder specific approaches, providing support for the efficacy of transdiagnostic treatments [16]. Given the large overlap between PPS syndromes, transdiagnostic interventions are needed, which can effectively target these factors to alleviate PPS, increase participation in life and reduce healthcare costs. Fig. 1 is a proposed logic model for this trial, and it illustrates the potential benefits of using a transdiagnostic approach for patients with PPS.

**Fig. 1 Fig1:**
[figure not shown]
Logic Model of PRINCE Secondary illustrating the potential benefits of using a transdiagnostic approach. MUS, Medically Unexplained Symptoms; NHS, National Health Service; WSAS, Work and Social Adjustment Scale; PHQ-9, Patient Health Questionnaire – 9 item Scale; GAD-7, Generalised Anxiety Disorder – 7 item Scale; PHQ-15, Patient Health Questionnaire – 15 item Scale

This paper presents a study protocol for the PRINCE (Persistent physical symptoms Reduction Intervention: a system Change and Evaluation in secondary care) Secondary trial, which aims to investigate the efficacy and cost-effectiveness of a therapist delivered transdiagnostic cognitive behavioural approach for treating patients with PPS in secondary care. Common transdiagnostic processes will be targeted with a view to bringing about a change in functional impairment and therefore will be measured alongside primary and secondary outcomes. These transdiagnostic process have been previously found to mediate change in chronic fatigue and chronic pain [17–19].

## Main research question

What is the efficacy and cost-effectiveness of a therapist delivered, transdiagnostic CBT intervention plus standard medical care (SMC) versus SMC alone for the treatment of patients with PPS in secondary medical care?

## Research objectives

### Primary objectives

To assess the efficacy of a therapist delivered, PPS specific (i.e. transdiagnostic) CBT intervention plus SMC for improving daily functioning in patients with PPS compared to SMC alone at 52 weeks after randomisation.

### Secondary objectives

To estimate whether therapist delivered transdiagnostic CBT plus SMC has a positive impact on symptom severity, mood and self-reported experience of the main symptom compared to SMC alone at 9, 20, 40 and 52 weeks post randomisation.To estimate the cost-effectiveness of therapist delivered transdiagnostic CBT plus SMC versus SMC alone at 26 weeks prior-, as well as 9, 20, 40 and 52 weeks post randomisation.To evaluate patients’ self-rated global measure of change in health resulting from CBT plus SMC versus SMC alone at 9, 20, 40- and 52-weeks post randomisation.To assess changes in psychological distress caused by patient-defined self-rated main problems at 9, 20, 40- and 52-weeks post randomisation.To assess treatment fidelity of the manual-based CBT intervention and to determine the implications for potential rollout in the National Health Service (NHS) if there is evidence of a treatment effect.To investigate putative cognitive and behavioural mediators of change.

## Methods

### Trial design

A two-arm parallel group randomised controlled trial (RCT).

### Method

Three hundred and twenty-two patients with PPS will be individually randomised to CBT plus SMC versus SMC alone. Follow-up assessments will be conducted at 9, 20, 40- and 52-weeks post randomisation.

### Setting

This is a multi-centre trial. Treatment will take place at a hospital out-patient department or via telephone. Participants will be recruited from secondary care in London, UK. Clinics include rheumatology, cardiology, respiratory, neurology, gastroenterology, urology or other.

### Target population

#### Inclusion criteria

Adults aged 18-65 years with a diagnosis of PPS. PPS is defined as persistent bodily symptoms with no clear cut obvious organic cause [1].Scoring ≥10 on the Work and Social Adjustment Scale (WSAS);Able to read and write in English;Willing to complete all trial visits;Willing and able to give written informed consent.

#### Exclusion criteria

Active psychosis and/or factitious disorder;Headaches as their main and only PPS symptom (given the clinical complexity of differentiating headaches and migraine, headaches will be excluded)Non-epileptic seizures as their main and only PPS symptom. This is due to a large ongoing RCT evaluating a specific cognitive behavioural approach for Dissociative Seizures recruiting from some of the same clinics;Drug or alcohol dependence disorder;Use of benzodiazepines exceeding the equivalence of 10 mg diazepam per day;Being in receipt of or having received CBT interventions for PPS during the past year;Are at imminent risk of self-harm;Participated in PRINCE Primary study (Trial Registration Number: NCT02444520).

#### Withdrawal criteria

Participants will be withdrawn from the trial if there are any concerns regarding their consent. Participants can decide to withdraw from the study at any point of the trial, without stating a reason. The trial team will be informed if a participant decides to withdraw consent for research follow-up. Patients who discontinue their treatment but do not withdraw from the study will be followed up. Patient withdrawal forms will be used to record potential dropouts and where possible the reason for drop out.

### Planned intervention: Transdiagnostic cognitive Behavioural therapy

The intervention will consist of a maximum of 8 one-hour CBT sessions delivered by one of three qualified trial therapists over a period of 22 weeks. Ideally, CBT sessions will be delivered face-to-face every fortnight. Telephone/skype appointments will be offered in exceptional cases (e.g. for patients with mobility issues). The treatment approach will be transdiagnostic and will be flexible to accommodate the needs of the individual and specific issues associated with specific problems. Thus, it will focus on previously identified symptoms that are overlapping across patient groups included in the trial, as well as common cognitive and behavioural responses to symptoms. The treatment will be manualised to aid the standardisation of treatment delivery and facilitate a potential rollout within the NHS and other healthcare systems if found to be effective. CBT sessions will be structured according to four distinct stages: (1) engagement and rationale giving; (2) reducing avoidance by exposure techniques; (3) dealing with symptom-related cognitions and emotions; and (4) relapse prevention. Overall, the intervention aims to help patients to:
Develop an understanding of the relationship between cognitive, emotional, physiological and behavioural aspects of their problem,Understand factors that may be maintaining the problem,Learn how to modify behavioural and cognitive responses, which may be maintaining the problem,Engage in avoided activitiesAddress negative thoughts and illness attributions maintaining symptoms,Address emotional dysregulation, anxiety, low mood or low self-esteem, if present,Adopt a healthy sleep routine which often maintains symptoms and disrupts healthy living.Find ways of living with uncertainty

A therapy manual specifically designed for participants will supplement the content of CBT sessions and will act as an aid to the therapist (see Table 1 for a summary). However, the transdiagnostic approach will also be flexible to accommodate specific issues associated with specific problems. For example, participants with IBS may benefit from discussing bowel related problems.

**Table 1 Tab1:** Summary of patient manual: a transdiagnostic approach for PPS

Chapter 1: Explanation of PPS	Explanation of i) PPS), ii) commonalities between PPS conditions, iii) CBT.
Chapter 2: Making sense of PPS	The impact of PPS on psychosocial functioning.
	Making a link between symptoms, behaviours and thoughts.
Chapter 3: Goal setting	Identifying goals.
	Strategies: goal setting.
	Homework: self-help materials (e.g. goal sheets).
Chapter 4: Monitoring your daily life	Rationale for keeping daily diaries.
	Homework: Keeping daily diaries.
Chapter 5: Activity scheduling	Explanation and evaluation of how PPS can reduce activity.
	Benefits of increasing activities.
	Homework: Increasing pleasurable and enjoyable activities.
Chapter 6: Overcoming barriers to change	Strategies to increase motivation.
	The impact of stress on PPS.
	The benefits of being active.
	Strategies to reduce stress levels and increase energy levels.
	Explanation and identification of “boom and bust behaviour”.
Chapter 7: Managing unhelpful thoughts and behaviours	Identifying unhelpful thoughts and behaviours.
	Self-help strategies for managing unhelpful thinking and behaviours.
	Identifying sources of social support and unhelpful relationships.
	The importance of assertiveness.
	Strategies to become more assertive.
Chapter 8: Living with uncertainty & developing acceptance	Strategies to cope with uncertainty.
	Managing discomfort with acceptance.
Chapter 9: Improving sleep	Identifying sleep problems.
	Advice on sleep management.
	Homework: Sleep management worksheets.
Chapter 10: Responding differently	Refocussing attention and distraction.
	Basic stress management.
	Relaxation techniques.
Chapter 11: Managing and coping with difficult emotions	Identifying difficult emotions.
	Coping strategies to facilitate the management of difficult emotions.
Chapter 12: Managing progress and managing setbacks	The importance of maintaining progress.
	Strategies to facilitate the routine application of relevant strategies learned in the manual/during therapy.
	Setting short- and long-term goals.
	Strategies for managing setbacks.

### Therapists

Three trained CBT therapists (clinical behavioural therapist or clinical psychologists) will provide CBT sessions. All therapists will receive training prior to delivering the CBT intervention to participants and supervision will be provided throughout the therapy. In case of resignation/parenting leave of a therapist, we will recruit a replacement therapist as quickly as possible. If a CBT session is missed due to therapist planned annual leave, the therapist will attempt to fit in the missing sessions within the five-month treatment period, but no more than one session will take place in any 1 week.

### Therapy training

All therapists will have previously been trained in CBT. A half day training will be required for the delivery of the intervention. Thereafter, weekly meetings will be set up at the start to ensure that all therapists are able to conceptualise PPS appropriately. Therapists will be informed of the trial protocol which will include how to deal with any protocol violations and confidential storage of audio-recordings. They will keep records of the therapy sessions in accordance with the guidelines of the clinical service in which they work and in accordance with professional guidelines.

### Therapy supervision

All therapists will receive group supervision every month with the CI (TC). During supervision, therapists will have the opportunity to discuss clinical issues that are problematic or challenging. The CI will remain blind to the actual identification of the patient. In addition, the supervision will check that the manual is largely being followed and ensure that the quality of therapy is sustained.

### Treatment Fidelity

All therapy sessions will be audio-recorded for treatment fidelity during the trial. A proportion of audio-recordings will be analysed by two independent clinicians once the trial has been completed. A fidelity measure will be developed, which includes overall therapeutic alliance, CBT skills and overall therapist adherence to the manual.

### Intervention adherence

The therapist will record how many CBT sessions out of 8 the participants attended, whether they were face-to-face, or telephone consultations and the duration of each session attended. At the end of therapy, the therapist will also score how well the participant adhered to therapy, as well as rate on a session-by-session basis how well the participant adhered to homework tasks.

If participants do not attend a session, the CBT therapist will contact the participant by telephone to ascertain the problem regarding attendance and will discuss options regarding how to proceed. Choices include a telephone session or a re-arranged face-to-face session, so long as the latter is within five working days. Alternatively, the session will be recorded as having not been attended. Telephone sessions will be kept to a minimum and only arranged if circumstances do not allow the patient to attend the face-to-face session.

### Standard medical care

Patients in both trial arms will receive SMC. SMC is defined as the continuation of any follow-up consultations as planned with specialised medical staff, including investigations, discussion of the PPS diagnosis, and the prescribing of any medication if required.

### Recruitment

Recruitment of patients will be from secondary care outpatient clinics or if recruitment proves difficult GP surgeries will be approached*.* Medical practitioners will inform potentially eligible patients about the trial and provide them with a trial leaflet.

### Study procedure

Interested participants will be asked to sign an agreement to be contacted by the research team. The research team will then be responsible for screening patients to check eligibility for the trial as there will be no structured clinical interview prior to inclusion. Eligible patients will then be provided with verbal and written information on the trial to read through. To formally enrol, patients will be required to complete and return a signed informed consent form. Once consent is obtained, they will be asked to complete a baseline questionnaire pack within 1 month of screening. Participants will then be randomised to one of two arms: CBT plus SMC or SMC alone. Outcomes will then be determined at 9, 20, 40 and 52-weeks after randomisation. Fig. 2 provides a CONSORT diagram, outlining the journey of all participants through the trial.

**Fig. 2 Fig2:**
[figure not shown]
PRINCE Secondary CONSORT Diagram of Study Procedure

### Randomisation

Participants will be randomly allocated to one of two trial arms, using a web-based randomisation system managed by the King’s Clinical Trials Unit (KCTU). Randomisation will be at the level of the individual, using block randomisation with random block sizes, stratified by clinic (e.g., cardiology, neurology etc.) and disability level (moderately severe impairment or significant impairment) as indicated by the Work and Social Adjustment Scale.

Treatment allocation will be communicated by email to the trial manager within a period of 24 h. The trial manager will inform the participant of their treatment group by telephone/email that same day. Following allocation to the treatment group the trial manager will inform the therapist, who will contact the participant to arrange the first session.

### Proposed sample size

The sample size is based on a previous study: a RCT of rehabilitative treatments for chronic fatigue syndrome [20]. We used data from this trial as it also used the work and social adjustment as an outcome. Based on the White et al. study, we calculated a treatment effect of − 3.6 points on WSAS comparing CBT at 12 months. The within-group SD at 12 months was estimated to be 9.4 points giving a standardised effect size of Cohen’s d = 3.2/9.4 = − 0.38. The sample size calculation (Stata command sampsi) suggests that 161 patients per arm (322 in total) are needed to detect this effect size or a larger one with 90.14% power allowing for a deflation for including baseline measures in the analysis model (factor 0.84 assuming a correlation between baseline and 9-month WSAS of 0.4) and an attrition rate of 25%.

### Data management

Data management procedures and blinding will mirror the methods described in a primary care cluster randomised controlled trial [21]. This trial used the same quality assurance methods. In summary, self-report measures and therapy data will be entered onto the InferMed MACRO online database, hosted by the King Clinical Trial Unit (KCTU). This system is used for clinical trials that are managed by the Clinical trials Unit at the Institute of Psychiatry, Psychology and Neuroscience at King’s College London. It follows Good Clinical Practice and FDA 21 CFR Part 11 regulations.

Data entry and management will be undertaken by the research assistants and random checks will be undertaken by the trial manager. The Chief Investigator will be the custodian for the trial data. Patient data will be pseudo-anonymised (allocation of a unique personal identification number (PIN)) after randomisation. Data will be stored on a password-protected computer and in accordance with the General Data Protection Regulation (GDPR). Data will be archived and stored in line with requirements of the sponsor. Paper data will be stored in locked filing cabinets within a locked room and Department.

### Blinding

All data will be handled by the research team independent of the clinical team responsible for assessing and treating the patients. As this is a psychotherapy trial it is impossible to blind therapists and patients to which treatment they have been allocated to. Outcomes are all self-report measures and will be collected via post or email. Aside from the trial manger, the trial management team including the chief investigator, statisticians and the independent oversight committees will be blind to treatment allocation. If for any reason unblinding occurs the CI, TSC and DMEC will be notified.

### Data collection and follow-ups

Outcome measures will be collected at baseline (pre-randomisation) and at 9, 20, 40, and 52 weeks post-randomisation. Outcome measures will be collected during a time window and will be dependent on the follow-up time-point. Time windows will be as followed; 9 weeks – (time-window 7, 12); 20 weeks – (time-window 18, 35); 40 weeks – (time-window 38, 49); 52 weeks – (time-window 50, 63).

Participants will be asked to complete self-report measures either in writing, electronically via email or over the telephone. If participants decline to complete the full follow-up assessment but have not revoked their consent to be followed up, they will be asked to fill in only the primary outcome questionnaires. Participants who do not return their questionnaires will be contacted by the research worker via telephone/text/email, to remind them to post back their questionnaires or to invite them to complete them over the telephone.

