### Measures

All measures are summarised in Table 2.

**Table 2 Tab2:** Screening and data collection across the trial

	Completed by	Baseline	End of Therapy	9 weeks	20 weeks	40 weeks	52 weeks
ASSESSMENTS							
Primary Outcomes							
WSAS	P	X		X	X	X	X
Secondary Outcomes							
PHQ-15	P	X		X	X	X	X
PHQ-9	P	X		X	X	X	X
GAD-7	P	X		X	X	X	X
PPS Questionnaire	P	X		X	X	X	X
CGI-patient	P	X		X	X	X	X
CSRI	P	X		X	X	X	X
EQ-5D-5 L	P	X		X	X	X	X
Process Variables							
Therapy Process Indicators							
*Treatment Attendance and Homework Log*^b^	T						
*Treatment Adherence*^b^	T						
*Treatment Fidelity*	IC		X				
*Competence Rating*	IC		X				
Satisfaction with Treatment^a^	P				X	X	X
CGI-therapist	T		X				
PSYCHLOPS^a^	P	X		X	X	X	X
Mechanisms of Change							
*CBRQ*	P	X		X	X	X	X
*Acceptance Scale*	P	X		X	X	X	X
Baseline							
Demographic Variables	P	X					
Clinical Information	P	X					
Preferred Treatment Group	P	X					
Therapist Background Measures	T	X					
Other							
Concomitant Medications	P	X		X	X	X	X
Serious/Adverse Events	P				X	X	X

*WSAS* work and social adjustment scale, *PPS Questionnaire* persistent physical symptoms questionnaire, *PHQ-9* patient health questionnaire – 9 item scale, *GAD-7* generalised anxiety disorder – 7 item scale, *PHQ-15* patient health questionnaire – 15 item scale, *CGI* clinical global impression scale, *CBRQ* cognitive behavioural responses questionnaire, *CSRI* client service receipt inventory, *EQ-5D-5 L* EuroQol 5 Dimension 5 Level, *PSYCHLOPS* psychological outcome profiles, *P* patient, *IC* independent clinician, *T* therapist. ^a^ Assessment only completed by participants assigned to the intervention group. ^b^ completed after each therapy session

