#### Primary outcome measures

*Functional Impairment*: the Work and Social Adjustment Scale (WSAS) is a 5 item scale used to measure the extent to which people’s problems interfere with their ability to carry out normal activities, go to work, partake in private and social activities and impact on relationships [23]. It is a valid and reliable scale which was chosen as it is a routine outcome measure in Increasing Access to Psychological Therapies (IAPT). It has also been used in several other randomised controlled trials evaluating psychological interventions for IBS and CFS [20, 23, 24].

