### Procedures for recording and reporting serious adverse events

Adverse Events (AE) will be assessed at 20, 40 and 52 weeks after randomisation. All serious adverse events (SAE) and reactions (SAR) will be reported immediately to the Chief Investigator, sponsor and DMEC. AE’s that are defined as serious will mirror the criterion described in a primary care cluster randomised controlled trial [21].

In summary, the reporting of SAE’s will be based on the following criterion; (i) death of a participant, (ii) life threatening event (iii) hospitalisation (not including elective hospitalisation for pre-existing condition) (iv) deliberate self-harm or (v) any important medical condition which may influence the participants safety. In addition, an SAE will be reported, if the participant deteriorates in that the level of disability worsens and they are unable.to carry out important daily activities for more than 4 weeks.

All serious adverse events and reactions will be reviewed, by two members of the DMEC without the presence of the CI. If deemed necessary, the scrutinisers would then be unblinded to treatment allocation so that they can then establish whether any serious adverse events were serious adverse reactions to the transdiagnostic approach.

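### The reduced follow-up for participants who decline the full pack is the WSAS alone, which read literally drops the adverse event questions scheduled at weeks 20, 40 and 52

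*Protocol article*

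**What the plan says.** The protocol article, under Data collection and follow-ups, sets a fallback. It applies "If participants decline to complete the full follow-up assessment but have not revoked their consent to be followed up"; in that case "they will be asked to fill in only the primary outcome questionnaires".

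Table 2 (Measures) has one entry under primary outcomes, the WSAS. Under Primary outcome measures, "the Work and Social Adjustment Scale (WSAS) is a 5 item scale", and its description covers functional impairment only. The row "Serious/Adverse Events" stands elsewhere in Table 2, under the heading for other items. It is completed by the patient and marked at 20, 40 and 52 weeks.

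The section on recording and reporting serious adverse events says: "Adverse Events (AE) will be assessed at 20, 40 and 52 weeks after randomisation". It makes no exception for participants on the reduced follow-up. It adds: "All serious adverse events (SAE) and reactions (SAR) will be reported immediately to the Chief Investigator, sponsor and DMEC".

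**The concern.** The fallback is meant to save the primary outcome when a participant finds the full pack too much. As worded, it also removes the adverse event item. The people concerned are still in contact and have not withdrawn consent. Their WSAS enters the efficacy analysis, yet nobody is told to ask them whether they were admitted to hospital, harmed themselves or had another listed event.

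Two things are at stake. First, events in this group may not be recorded, and the missing-data approach under Statistical analysis is written for the outcome models; it cannot restore an event that was never asked about. Second, participants with WSAS data and participants with adverse event data become different sets. If adverse event counts are then set against everyone randomised, or everyone with a WSAS, the rate is too low by construction.

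**Working it through.** The document gives no figure for how many will use the short form, or for adverse event rates, so there is no stated number to reproduce. The main check is to set the sections side by side.

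**What each section requires of a participant on the reduced follow-up**

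| Week | Data collection and follow-ups (fallback) | Table 2, adverse event row | Safety section |
|---|---|---|---|
| 9 | WSAS only | not scheduled | not scheduled |
| 20 | WSAS only | patient-completed | assessed |
| 40 | WSAS only | patient-completed | assessed |
| 52 | WSAS only | patient-completed | assessed |

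The conflict is at weeks 20, 40 and 52. Nothing is lost at week 9.

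**Does another stated route close the gap?**
- The immediate-reporting duty says to whom a known event is passed on. It does not say how an event is found.
- Outcomes are self-reported and collected by post, email or telephone (Blinding; Data collection and follow-ups), so no research visit is scheduled at which an event would come to light.
- The CSRI asks about health service use (Secondary outcome measures) and could have revealed an admission, but the short form drops it too.
- The WSAS is kept and overlaps with one criterion: "an SAE will be reported, if the participant deteriorates in that the level of disability worsens". That criterion also requires more than 4 weeks of being unable to carry out important daily activities. No rule links a WSAS score to it.
- Therapists see CBT participants for at most 8 sessions and may hear of events by chance. Participants in the SMC arm have no trial therapist. The patient form is the only route in Table 2 that applies to both arms alike.

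**How large could it be? Illustration on assumed inputs**

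Let f be the share of participants on the short form and r their risk of an event relative to the rest. Assume that everyone else is asked and that there is no other detection. Neither f nor r is in the document.

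Share of participants with events who are not asked = f·r / (f·r + 1 − f).

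| f | Number of 322 | r = 0.5 | r = 1 | r = 2 |
|---|---|---|---|---|
| 5% | 16.1 | 0.025/0.975 = 2.6% | 5% | 0.10/1.05 = 9.5% |
| 10% | 32.2 | 0.05/0.95 = 5.3% | 10% | 0.20/1.10 = 18.2% |

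**Effect of the denominator**, with f = 10%, as the ratio of observed to true event rate:
- Over all randomised: 0.90/(0.90 + 0.10·r). This gives 0.90 at r = 1 and 0.90/1.10 = 0.82 at r = 2.
- Over those asked: 1/(0.90 + 0.10·r). This gives 1.00 at r = 1, 1/1.10 = 0.91 at r = 2, and 1/0.95 = 1.05 at r = 0.5.

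So the right denominator removes the error when r = 1 and reduces it at r = 2. Otherwise the sign depends on r. Distortion of the comparison between arms further depends on whether f and r differ by arm.

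**The case against.** The strongest reply is that the fallback sits in a paragraph about outcome measures, so its limit may apply to outcome scales only, leaving the safety section's schedule intact. The article is also condensed: the safety section presents its criteria as a summary and refers to another trial. It lists death as a serious event, which no participant can self-report, so the investigators must expect some events to arrive by other means. All this is fair. It rules out calling the patient form the only source of safety data, and it means the omission may be one of wording rather than of practice. It does not settle the matter: the fallback is a stated rule, not a silence, and staff who follow it would not ask. The reference to the other trial is for what counts as serious, not for how events are found.

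A reader might go further and infer three things that the document does not support.
- That decliners are the people most likely to have been harmed. No section says so. Questionnaire burden is as plausible, and the rule applies in both arms. The Statistical analysis section treats missingness as possibly related to adherence, but that is a question to be tested.
- That the sample size assumption of "an attrition rate of 25" per cent measures the loss. That figure is overall attrition. It is not the share using the short form, and participants who return nothing would be lost to safety whatever the short form contains.
- That reminder calls carry no safety question. The article gives the purpose of these calls, not their content, and a call script is something an article normally leaves out.

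**Conclusion.** The point holds as an inconsistency with a practical consequence. Read literally, the reduced follow-up omits the serious/adverse event item at weeks 20, 40 and 52, while the safety section promises assessment at those weeks without exception. No other systematic route for finding events in these participants is stated. Safety data may thus be lost by rule in people who remain reachable and count for efficacy.

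The size is unknown. The illustrative range of 2.6% to 18.2% of participants with events not being asked rests wholly on assumed values (5% or 10% on the short form, relative risk 0.5 to 2) and on there being no other detection. Neither the size nor the direction of any bias can be read from the document, and it does not show that the recorded safety data would be favourably selected. The change is worth making because it is cheap and the information is hard to recover later. The primary efficacy analysis is not affected.

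**What to change.** Amend Data collection and follow-ups so that the minimum dataset for participants who decline the full assessment is the WSAS at every follow-up, plus the serious/adverse event questions at weeks 20, 40 and 52. The questions should be put to the participant, in the same form in both arms. If the fallback was meant to limit outcome scales only, one added clause to that effect reconciles it with the safety section.

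Report, by arm and time point, the number of participants with adverse event data, and use that number as the safety denominator beside the event counts.

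The cost is a few more questions for people who have already declined a longer form, with some risk that a few will then not return the WSAS; placing the WSAS first limits that. Beyond this it needs a small amendment to the protocol and the short form, and no new visits.
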